## Abstract

**Background:**

Knowledge of HIV status remains below target in sub-Saharan Africa, especially among men and adolescents. HIV self-testing (HIVST) is a novel approach that enables unique distribution strategies, with potential to be highly decentralised and to provide complementary coverage to facility-based testing approaches. However, substantial gaps in evidence remain on the effectiveness and cost-effectiveness of HIVST, particularly in rural settings, and on approaches to facilitate linkage to confirmatory HIV testing, prevention, and treatment services. This protocol describes two cluster-randomized trials (CRT) included within the UNITAID/PSI HIV Self-Testing Africa (STAR) project.

**Methods:**

Two independent CRTs were designed around existing reproductive health programmes in rural Malawi and rural/peri-urban Zambia. Common features include use of constrained randomisation to allocate health clinic catchment areas to either standard HIV testing (SOC) or SOC plus community-based distribution of OraQuick HIV Self Tests (Bethlehem, PA USA, assembled in Thailand) by trained lay distributors selected by the community. Community-based distribution agents will be trained (3-day curriculum) to provide brief demonstration of kit use and interpretation, information and encouragement to access follow up services, and management of social harm.

The primary outcome of both CRTs is the proportion of the population aged 16 years and older who tested for HIV within the 12-month intervention period. Secondary outcomes in both trials include lifetime HIV testing, antiretroviral therapy (ART) initiation and ART use. Circumcision status among males will be a secondary outcome in Zambia and clinic-level demand for ART will be a secondary outcome in Malawi. Outcomes will be measured using cross-sectional household surveys, and routine data extraction from participating clinics. Costing studies will be used to evaluate the cost-effectiveness of the intervention arm. Qualitative research will be used to guide distribution and explore reasons for testing and linkage to onward care.

**Discussion:**

The STAR-Malawi and STAR-Zambia trials will provide rigorous evidence of whether community-based lay HIVST distribution is an effective and cost-effective approach to increasing coverage of HIV testing and demand for follow-on HIV services in rural and peri-urban communities in sub-Saharan Africa.

**Trial registration:**

Clinicaltrials.gov, Malawi: NCT02718274, 18 March 2016; Zambia: NCT02793804, 3 June 2016. Protocol date: 21 February 2018.

## Background

Knowledge of HIV status remains low in many parts of sub-Saharan Africa, particularly among men and adolescents (aged 10–19) [1]. As a gateway to treatment and prevention services, HIV testing is key to achieving United Nation’s (UN) 2020 fast track targets [2, 3]. However, recent population-based data from Malawi and Zambia show that the percent of people with HIV (PHIV) who know their status is far lower than the 90% benchmark set by the UN, with only 73% of PLHV in Malawi and 67% of PLHIV in Zambia aware of their status in 2015 [4, 5]. Despite integration and decentralisation of facility-based HIV testing services in antenatal care, tuberculosis clinics and primary care, as well as community-based outreach to reach remote and under-served communities, knowledge of status remains low [6, 7]. To overcome these gaps and achieve the UN testing targets, novel and affordable approaches are needed.

HIV self-testing (HIVST) has potential to increase accessibility to and uptake of HIV testing, particularly among populations not well-served by existing HTS. In HIVST, individuals collect their own specimen, conduct their own test, and interpret their own result. In 2016, the World Health Organization (WHO) recommended HIVST as a way to expand HTS services, particularly to high risk and underserved populations [8]. Early studies in Malawi and elsewhere have shown HIVST to be acceptable, and that oral fluid HIVST kits can be performed accurately, especially when provided with a brief in-person or video demonstration along with instructions-for-use provided by the manufacturer [9–11].

HIVST may provide more readily affordable and sustainable community-based HTS than existing models [12, 13]. Cost-effectiveness was shown for a community-based HIVST study in urban Malawi [14, 15]. Despite the potential impact of HIVST, evidence concerning cost-effectiveness for rural communities is limited. Few data to inform evidence-based choices between different HTS options for encouraging timely linkage to confirmatory testing and prevention and treatment services.

The Unitaid/PSI STAR (HIV Self-Testing Africa) project was developed to strengthen the evidence base around the effective use of HIVST in sub-Saharan Africa. STAR includes the design, implementation, and evaluation of a variety of HIVST distribution models and post-test linkage strategies. STAR also promotes the development of regulatory and policy environments enabling distribution of quality-assured HIVST kits. This protocol describes two CRTs within the STAR project assessing the effectiveness and cost-effectiveness of community-based HIVST distribution models in Malawi and Zambia.

### Study objectives

The overall objective of these trials is to evaluate the effectiveness of distribution of oral-fluid HIVST kits by community-based distribution agents (CBDA) on uptake of HIV testing, including coverage of recent (within 12 months) and lifetime testing among the population ages 16 years and older, and on ART initiation. The Zambia study also assesses the impact of self-testing on men’s circumcision status, and the Malawi study evaluates differences between arms in linkage to ART (offered routinely under a “test-and-start” strategy by the Government of Malawi) through extraction of clinic-level ART initiation data. Formative research, consisting of qualitative studies and discrete choice experiments (DCEs), will inform the final intervention design, training materials, social harms definitions. Procedures for reporting social harms related to the intervention are informed by qualitative research in each setting. Qualitative research and DCEs will also be used to maximise preferences for service configurations offered for testing and linkage, and to understand participant experiences. Costing studies and a cost-effectiveness analysis of the interventions will also be conducted.

Specific hypotheses tested by the trials include that community-based distribution of HIVST kits will increase:the proportion of the population who have tested for HIV within the past 12 months;the proportion of the population who have ever tested for HIV;the rate of ART initiations in clinics serving populations that received HIVST distribution.

## Methods and design

### Settings

CRTs will be conducted in rural settings in Malawi (Blantyre, Machinga, Mwanza and Neno districts) and rural, urban and peri-urban settings in Zambia (Ndola, Kapiri Mposhi, Lusaka and Choma districts). (Tables 1 and 2 provide additional information on the study sites).

**Table 1 Tab1:** HIV STAR-Malawi study clinics

District	Clinic name	Clinic Catchment Population (2014–2015)	Total HIV tests (2014–2015)	Percent HIV-positive tests (Number of positive tests / total tested at clinic 100%)	Allocation
Blantyre (N)	Chikowa Health Centre	34,317	4128	8.0%	HIVST
Blantyre (N)	Dziwe Health Centre	18,430	1794	7.6%	SOC
Blantyre (N)	Lirangwe Health Centre	27,880	3268	14.4%	SOC
Blantyre (N)	Makata Health Centre Lunzu	37,000	3502	6.9%	SOC
Blantyre (S)	Madziabango Health Centre	15,000	2281	7.2%	HIVST
Blantyre (S)	Mpemba Health Centre	23,600	5027	10.9%	HIVST
Blantyre (S)	Pensulo Health Centre	19,172	706	9.8%	SOC
Blantyre (S)	Soche Maternity	16,208	784	13.6%	HIVST
Machinga	Chikweo Health Centre	82,581	6938	6.8%	HIVST
Machinga	Mangamba Health Centre	22,364	5344	6.1%	HIVST
Machinga	Mbonechera Health Centre	112,934	1195	7.6%	SOC
Machinga	Mkwepere Health Centre	19,317	2715	6.6%	SOC
Machinga	Namanja Health Centre	34,678	3930	6.8%	HIVST
Machinga	Nayuchi Health Centre	21,582	2642	11.5%	SOC
Machinga	Ngokwe Health Centre	40,778	7165	5.3%	SOC
Mwanza	Kunenekude Health Centre	12,085	2758	4.9%	HIVST
Mwanza	Thambani Health Centre	19,056	2561	5.0%	SOC
Mwanza	Tulonkhondo Health Centre	16,700	2261	4.1%	SOC
Neno	Chifunga Health Centre	11,250	1994	6.0%	HIVST
Neno	Ligowe Health Centre	15,025	2118	5.0%	SOC
Neno	Luwani Health Centre	4452	1027	5.3%	HIVST
Neno	Magareta Health Centre	7547	1550	3.4%	HIVST

**Table 2 Tab2:** HIV STAR-Zambia study clinics

Pair	District	Community	Type of community (rural/peri-urban)	Distribution models	Population (2016)	Distance to district medical office in km	Allocation
1	Choma	Mbabala	Rural	Community, facility, VMMC	11,415	33	HIVST
1	Choma	Mapanza	Rural	Community, facility, VMMC	14,528	75	SOC
2	Choma	Batoka	Rural	Community, facility, VMMC	15,566	33	HIVST
2	Choma	Sikalongo	Rural	Community and facility	13,491	66	SOC
3	Kapiri Mphoshi	Chankomo	Rural	Community and facility	15,228	55	SOC
3	Kapiri Mphoshi	Nkole	Rural	Community, facility, VMMC	15,365	34	HIVST
4	Kapiri Mphoshi	St Pauls	Rural	Community and facility	7673	90	SOC
4	Kapiri Mphoshi	Mpunde	Rural	Community, facility, VMMC	15,694	48	HIVST
5	Lusaka	Ng’ombe	Peri-urban	Community, facility, VMMC	45,999	8	HIVST
5	Lusaka	Makeni	Peri-urban	Community and facility	51,264	9	SOC
6	Ndola	Lubuto	Peri-urban	Community, facility, VMMC	53,249	8	SOC
6	Ndola	Twapia	Peri-urban	Community, facility, VMMC	24,078	9	HIVST

### Study design

Using a parallel arm design, clinics will be randomly allocated either to receive community-based HIVST distribution in a defined catchment area, or to continue with usual clinic-based HTS (standard of care [SOC]). Clinic catchment areas will be randomized rather than individual testers because the intervention was designed to be delivered by community-based distributors. Individual-level randomization would therefore be inappropriate.

In Malawi, 22 rural primary health clinics will be randomized 1:1 to receive the HIVST intervention or SOC. Within the HIVST intervention arm, CBDAs will also be randomized 1:1 to provide either referrals to home-based ART initiation or the usual referrals to the clinic. Each clinic will contain a pre-defined, concentrated area of implementation, with two villages in each area selected for the baseline and endline household surveys, respectively.

In Zambia, 12 primary health clinics in 4 districts will be pair-matched within districts by distance to the district medical office and catchment area population, and randomized 1:1 to provide the HIVST intervention or SOC.

### Intervention and standard of care

Both trials will assess the effectiveness of community-distributed HIVST on HIV testing uptake using OraQuick HIV Self Tests (Bethlehem, PA USA, assembled in Thailand) including instructions-for-use translated by the manufacturer into local languages (Chichewa in Malawi; and Nyanja, Tonga, and Bemba in Zambia). The specificity and sensitivity of the test kit in a general rural population in sub-Saharan Africa will be assessed in separate studies [16]. HIVST kits will be stored and distributed by Population Services International (PSI)-Malawi or Society for Family Health (SFH)-Zambia. In both trials, CBDAs will be trained by PSI or SFH in how to explain the written self-test instructions, demonstrate correct use, and show examples of reactive and non-reactive tests to assist in reading results. Distributors will also be trained on appropriate test kit storage and information concerning linkage to confirmatory testing and ART for clients with reactive HIVST results or prevention for clients with non-reactive results. Clients will be offered the choice of testing with CBDA assistance or in private. CBDAs will also be trained in how to pre-empt, respond to and report social harm, including suicide, gender-based violence, or coerced testing. Individuals are eligible for HIVST if they are ages 16 years or older.

In Malawi, CBDAs will provide door-to-door community-based distribution of HIVST kits as well as access from their own homes, building on a pre-existing initiative providing reproductive health products. CBDAs will provide all clients who wish to test with: (1) information on the test and a demonstration on how to open and use the HIVST kit; (2) an envelope and short anonymous questionnaire to be completed by the client and returned with the kit; and (3) a self-referral form to facilitate linkage into HIV care and prevention services. CBDAs will distribute one test per resident who is interested in testing. CBDAs will visit clients after distributing the kit to enquire whether the kit has been used, collect the sealed questionnaire and used kit, and provide advice on referral to additional care if the client discloses a reactive HIVST result. Clients will also be able to drop used kits in locked boxes within each community, or return them to CBDAs at their homes.

CBDAs will be paid MWK 100 (USD 0.15) for each test kit distributed, and an additional bonus (MWK 50, or USD 0.08) for facilitating onward linkage to health services for clients with reactive HIVST results.

#### Malawi – Home-based ART intervention

In a second-stage randomisation, CBDAs working within clinic catchment areas allocated to the intervention (HIVST) will be randomly allocated to either no additional intervention, or HIVST plus the offer of home-based confirmatory testing, WHO staging, TB symptom screening and initiation of HIV care including a 4 week supply of ART and cotrimoxazole and a government ART patient card for service continuation at the nearest clinic. HIVST clients will need to confide their reactive self-test result with the CBDA, who will then arrange a single home visit by PSI nurses within seven days. This builds on a successful urban intervention of similar design [17].

#### Zambia – HIVST intervention

In Zambia, multiple modes of HIVST distribution will be provided to the catchment population of each intervention facility in addition to a similar CBDA model to Malawi. Healthcare workers will distribute HIVST within health facilities, while CBDAs will visit households to dispense HIVST kits. Voluntary male medical circumcision (VMMC) mobilizers employed by PSI are associated with some but not all facilities, and in intervention areas will distribute self-test kits as part of their activities. Distribution modes for each clinic are listed in Table 3. As in Malawi, clients who agree to HIVST will receive a demonstration of kit use; an envelope for the used kit and anonymous self-complete questionnaire to return with kit; and a self-referral card to the health facility to assist with linkage to confirmatory testing and care as needed. Boxes to return used self-test kits will be located at each facility as well as in public areas in the community, and used kits can be returned to CBDAs.

**Table 3 Tab3:** Primary and secondary outcomes of HIV STAR-Zambia and HIV STAR-Malawi impact evaluations

Outcome	Trial	Data source
Primary outcome – community HIVST distribution		
Tested for HIV within past 12 months	Malawi, Zambia	Self-report, endline household survey
Secondary outcomes – community HIVST distribution		
Ever tested for HIV	Malawi, Zambia	Self-report, endline household survey
ART initiation 6 months and 12 months after distribution begins	Malawi, Zambia	Routine data extracted from clinic
Current ART use	Zambia	Self-report, endline household survey
Circumcision within past 12 months (men only)	Zambia	Self-report, endline household survey
Primary and secondary outcome – home-based distribution (Malawi only)		
Primary: Disclosure of a positive results to the CBDA during months 1 to 12 of intervention	Malawi	CBDA post-test log book
Secondary: ART initiation between months 1 and 12 of the intervention	Malawi	Routine data extracted from clinic

CBDAs will be recruited from the communities in which they will work, and will have previously worked with the health facilities included in the impact evaluation. CBDAs and VMMC mobilisers will be paid using a performance-based structure (ZMW 5/distributed kit and ZMW 2.5/used kit returned, or USD 0.56 and 0.28).

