### Economic analyses

#### Costing and cost effectiveness studies

The costing analysis will estimate the societal-level costs of community distribution of HIVST, both from the perspective of the health provider and the user, and will compare the costs of community HIVST distribution with standard HTS. The costing study will feed into estimates of cost-effectiveness, which will be projected on different time scales and population levels.

Full financial and economic costs from the providers’ perspective will be collected from PSI/SFH and from public health care facilities. User costs of accessing existing and new forms of HIV testing and linkage to care will be gathered using the extended baseline and endline questionnaires. Costing tools will be used in conjunction with service-related financial and activity reports in order to determine the unit costs of providing HTS and subsequent HIV care. We will also carry out detailed micro-costing, including time and motion studies, to clinics assigned to the intervention and control arms of the impact evaluation. This will help to identify instances of reduced crowding in ART clinics due to HIVST decentralisation. Gathered costing data will be used to conduct an economic evaluation, using decision-analytic modelling, to compare the costs of the different HIVST models to standard HTC models. Key outcomes will include the incremental cost per Disability Adjusted Life-Year (DALY) averted, which will allow the cost-effectiveness of HIVST and linkage to care models to be determined.

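### In Zambia the trial tests a multi-channel HIVST package, but the objective, outcome labels and planned conclusion describe community distribution by lay agents

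*Protocol article*

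**What the plan says.** Several parts of the protocol article describe one intervention for both trials.

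- Study objectives: the overall aim of the two trials is to "evaluate the effectiveness of distribution of oral-fluid HIVST kits by community-based distribution agents (CBDA) on uptake of HIV testing". The hypotheses that follow are also about community-based distribution.
- Abstract, Methods: among the common features is the comparison of standard of care with standard of care plus community distribution "by trained lay distributors selected by the community".
- Study design: "clinics will be randomly allocated either to receive community-based HIVST distribution in a defined catchment area, or to continue with usual clinic-based HTS".
- Intervention and standard of care: "Both trials will assess the effectiveness of community-distributed HIVST on HIV testing uptake".
- Table 3: the primary and secondary outcomes, including those specific to Zambia, stand under headings that call the intervention community HIVST distribution.
- Abstract, Discussion: the two trials are to show "whether community-based lay HIVST distribution is an effective and cost-effective approach".

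The section on the Zambia HIVST intervention describes something wider. Each intervention facility's catchment gets several distribution modes on top of a CBDA model like Malawi's: "Healthcare workers will distribute HIVST within health facilities, while CBDAs will visit households to dispense HIVST kits". VMMC mobilisers, who are attached to some facilities but not all, also distribute kits in intervention areas. The standard-of-care section describes no kit distribution.

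**The concern.** The randomised contrast in Zambia does not match the intervention named in the objective and the conclusion. Handing out kits inside a clinic through health workers is a different delivery model from door-to-door distribution by lay agents. If the plan is followed as written, a positive Zambia result will be reported as evidence for community lay distribution, although kits from the other channels may have produced part of it.

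This matters for use of the results. The article's closing Discussion says that ministries will draw on them for national testing plans and that they will feed into WHO guidance. A programme that adopted CBDA distribution alone could not assume that it would obtain the Zambia effect. The Zambian circumcision outcome is also exposed: it carries the community-distribution label, yet circumcision mobilisers are among those giving out kits.

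**Working it through.** The article gives no figure on this point to reproduce. The check is whether the randomised comparison can identify the quantity named in the objective.

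1. **Target.** Study objectives: the effect on testing of kit distribution by CBDAs.
2. **Intervention arm in Zambia.** Zambia HIVST intervention section: CBDA visits, plus health-worker distribution in facilities, plus VMMC mobilisers where present. The added modes apply to the catchment of every intervention facility. With 12 clinics randomised 1:1, that is 12 / 2 = 6 clusters. No cluster is described as receiving CBDA distribution only.
3. **Control arm.** Standard of care section: HIV testing and ART initiation under national guidelines.
4. **Outcome.** Outcome evaluation and measurement: any HIV test within 12 months of the start of the intervention, whatever the source of the kit or test.
5. **Analysis.** Trial analysis: cluster-level summaries compared between whole arms, with no component for distribution mode.

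Write Y(package) for mean coverage under all the Zambian channels, Y(CBDA) for coverage under CBDA distribution alone, and Y(SOC) for coverage under standard of care. Then

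Y(package) − Y(SOC) = [Y(CBDA) − Y(SOC)] + [Y(package) − Y(CBDA)].

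The trial estimates the left-hand side. The objective asks for the first bracket on the right. Since no randomised cluster is assigned to CBDA distribution alone, Y(CBDA) is not observed and the two brackets cannot be separated. Any split is compatible with the same trial result.

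Table 2 is weak support for step 2. Tabulating its distribution-mode column by allocation gives:

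| Allocation | Community, facility and VMMC | Community and facility |
|---|---|---|
| HIVST | 6 of 6 | 0 of 6 |
| SOC | 2 of 6 | 4 of 6 |

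The column lists modes for the standard-of-care clusters as well, without explanation, so it cannot be read simply as channels delivered. The argument therefore rests on the text of the Zambia section. (That section refers the reader to Table 3 for the modes; they are in Table 2.)

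Malawi is not affected. There the kits come from CBDAs, door to door and from their own homes, which matches the objective.

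**The case against.** The strongest reply is that a package is a legitimate intervention for a short, pragmatic evaluation, and that the article discloses it openly under a separate Zambia heading. The trials are called independent, each country is analysed separately and no pooled estimate is planned. All of this stands, and the Zambia comparison remains valid for the package. But one paragraph of disclosure does not correct an objective, outcome headings and a conclusion that name a different intervention.

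A second reply is that monitoring data, kit barcodes and endline questions on CBDA visits and kit receipt will show the CBDA contribution. They can describe it, without randomisation. The survey contents are posted online and not shown here, so a question on kit source may already exist, and nothing should be inferred from its not being mentioned.

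A reader might infer that cost-effectiveness in Zambia would look too good, because the costing section opens with the aim to "estimate the societal-level costs of community distribution of HIVST". The documents do not support that. The same section collects provider costs from PSI/SFH and from public facilities and compares the different HIVST models with standard testing, and Table 4 lists the costs of distribution models. The VMMC mobilisers are employed by PSI, so their costs appear to be covered. What is missing is only an explicit statement that the package effect is paired with the cost of all channels.

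It is also open whether VMMC mobilisers count as community distributors: the article does not exclude them and pays them on the same basis as CBDAs. Only the facility channel clearly falls outside the label. Finally, the article's closing Discussion speaks of community-based distribution without mentioning lay agents or CBDAs; the explicit lay claim is in the Abstract's Discussion.

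**Conclusion.** The point holds as a mismatch between the Zambian intervention and the claim made for it. The Zambia trial estimates the effect of a multi-channel HIVST package against standard of care and gives no randomised estimate for CBDA distribution alone. The mismatch covers the whole Zambian intervention arm. It rests on reading the Zambia section as describing what is delivered at every intervention facility, with VMMC distribution only where mobilisers are present.

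No numerical size of the misattribution can be derived. A reader might be tempted to assume a share of kits from other channels and apply it to the 25-point planning difference (50% × 1.5 = 75%; 75 − 50 = 25). The documents give no such share, the 25 points are a detectable difference and not an expected effect, and the product would require channel effects to add up, although a person reached through one channel might otherwise have tested through another. Nor does the point make the Zambia trial biased or uninformative. The randomisation, outcome and analysis are sound for the package question.

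**What to change.** 1. Restate the Zambia objective, hypotheses, Table 3 outcome headings and planned conclusion as the effect of the combined package (CBDA, facility and, where present, VMMC mobilisers) against standard of care. Limit any conclusion about CBDA or community lay distribution alone to Malawi.
2. Report Zambian self-testing by kit source (CBDA, health worker, VMMC mobiliser) from the endline survey and monitoring data, labelled as a non-randomised description. Add a kit-source item to the survey if it is not already there.
3. State that the Zambia cost-effectiveness estimate pairs the package effect with the cost of all channels.
4. Explain what the distribution-mode column in Table 2 means for standard-of-care clusters, and correct the table reference in the Zambia section.

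The cost is wording, at most one survey item and a descriptive table. Randomisation, sample size and the primary analysis are unchanged. The downside is a narrower Zambia claim.

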### Randomization

The Malawi trial includes two stages of randomization. In the first stage, clinic catchment areas will be allocated to HIVST or standard of care arms using restricted randomization. To ensure that intervention and standard of care clinics are evenly distributed geographically across the study area, we will restrict the number of intervention clinics in each district, with larger districts to include at least 35% intervention clinics. We will balance arms in terms of number of testers, proportion of positive tests, and total catchment population across clinics. The study statistician (MN) provided a list of 1000 eligible randomization combinations to the study team and the final randomization scheme was selected in a public ceremony in Blantyre, Malawi on 21 March 2016.

In the second-stage randomization, we will randomize all CBDAs providing HIVST to home-based initiation of ART or standard of care at a 1:1 ratio. CBDAs will be randomized in blocks of varying sizes from 2 to 12 CBDAs, with the distribution of block sizes following Pascal’s triangle (i.e., 1:5:10:10:5:1).

In Zambia, clinics will be randomized 1:1 within matched pairs to receive the HIVST intervention or standard of care. Randomization was conducted by the statistician (BH) and was completed on 24 June 2016.

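### Zambia: VMMC is listed for all six HIVST communities but only two of six SOC communities, so a circumcision difference cannot be credited to self-testing alone

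*Protocol article*

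**What the plan says.** Study objectives in the protocol article gives the Zambian circumcision aim: "The Zambia study also assesses the impact of self-testing on" men's circumcision status. Table 3 makes self-reported circumcision in the past 12 months a secondary outcome for Zambia, measured in the endline household survey. Outcome evaluation and measurement repeats this.

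Zambia – HIVST intervention describes several ways of handing out kits. Of one it says: "Voluntary male medical circumcision (VMMC) mobilizers employed by PSI are associated with some but not all facilities"; where the intervention is delivered, these mobilisers also hand out kits. The section sends the reader to Table 3 for each clinic's distribution modes, but they stand in Table 2, where each Zambian community is entered as "Community, facility, VMMC" or "Community and facility". SOC communities have entries too.

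Study design says the clinics are "pair-matched within districts by distance to the district medical office and catchment area population". Randomization says that "clinics will be randomized 1:1 within matched pairs to receive the HIVST intervention or standard of care", and that this was completed on 24 June 2016. Trial participants and procedures mentions matching only on population served and, for peri-urban sites, distance.

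Trial analysis gives clusters equal weight and compares log-transformed cluster values by arm. It allows second-stage regression on cluster-level factors if this is thought necessary, and names none. Table 4 shows that circumcision status is recorded in the baseline survey.

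**The concern.** The job title suggests that VMMC mobilisers exist to bring men to circumcision, so their presence is a likely direct cause of this outcome. If they work in every HIVST community and in a third of the SOC communities, a higher rate of recent circumcision in the HIVST arm could come from kits, from mobilisers, or from both. The stated objective would credit all of it to self-testing.

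The Discussion expects the results to feed national testing plans and WHO guidance. A circumcision effect credited to self-testing could therefore be carried to places without mobilisers, where it might not appear.

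**Working it through.** The document gives no sample size or power for circumcision, so there is no stated figure to reproduce. The check is a count from Table 2, followed by what the count implies.

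**1. Count by pair (Table 2)**

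| Pair | HIVST community | VMMC listed | SOC community | VMMC listed |
|---|---|---|---|---|
| 1 | Mbabala | yes | Mapanza | yes |
| 2 | Batoka | yes | Sikalongo | no |
| 3 | Nkole | yes | Chankomo | no |
| 4 | Mpunde | yes | St Pauls | no |
| 5 | Ng'ombe | yes | Makeni | no |
| 6 | Twapia | yes | Lubuto | yes |

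VMMC is listed for 6/6 HIVST and 2/6 SOC communities. Pairs 2, 3, 4 and 5 are discordant, all in the same direction. Pairs 1 and 6 are concordant.

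**2. Could this be chance?** If mobilisers were in place before allocation, each discordant pair falls either way with probability 1/2. All four falling towards HIVST has probability (1/2)^4 = 1/16 = 0.0625, or 0.125 for either direction. That is compatible with chance.

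**3. Size of the mixing.** Suppose self-testing has no effect and mobilisers multiply a community's circumcision rate by m. With equal weights and logs, each discordant pair contributes log m and each concordant pair contributes 0. The mean log ratio is (4/6) log m, so the apparent arm ratio is m^(4/6). The values of m are assumptions; the document gives none.

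- m = 1.25: 1.25^(4/6) = 1.16
- m = 1.5: 1.5^(4/6) = 1.31
- m = 2.0: 2.0^(4/6) = 1.59

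**4. What adjusting for mobilisers would cost, pairs kept.** Write each within-pair log difference as a + b·x, with x = 1 in pairs 2 to 5 and x = 0 in pairs 1 and 6. The adjusted arm effect a is the mean of pairs 1 and 6 only.

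- Variance: 1/2 of the pair-difference variance, against 1/6 without adjustment, so 3.0 times as large.
- Residual degrees of freedom: 5 to 4, with t(0.975) going from 2.571 to 2.776.
- Confidence interval width at the same residual SD: √3 × 2.776/2.571 = 1.87 times.

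**5. The same, pairs ignored.** The correlation between arm and VMMC is (6×4 − 0×2)/√(6×6×8×4) = 0.71. The variance is multiplied by 1/(1 − 0.5) = 2.0, degrees of freedom go from 10 to 9, and the interval is about 1.44 times as wide.

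**The case against.** The Table 2 column describes distribution models, not mobiliser presence, and the document never says whether its entries date from before randomisation. If mobilisers predate allocation, the imbalance is one that randomisation can produce. If they came with allocation, they are one of the distribution modes and so part of the intervention. Cluster-level adjustment is permitted, and naming covariates for a secondary outcome is commonly left to an analysis plan, which is not shown. The multipliers have no source in the document.

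Much of this stands. The column's meaning is an inference, though a well-supported one: SOC communities are to distribute no kits, yet their entries differ, and the text ties mobilisers to facilities and has them give out kits only in intervention areas. The missing covariate is not itself the fault. But under either account of timing, the six-pair contrast does not isolate self-testing, and the objective is worded as if it did.

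A reader might infer more, in three ways that the document does not support:

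- That the circumcision outcome can tell us nothing about self-testing, or that randomisation failed. Chance can explain the imbalance, and an adjusted estimate exists, however imprecise.
- That the outcome cannot be measured, because Table 4 lists only circumcision status. Table 4 is an overview, and Outcome evaluation and measurement says recent circumcision is collected at endline.
- That mobilisers also inflate the primary testing outcome. Nothing in the document says that men are tested for HIV at VMMC services.

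**Conclusion.** The point holds in a limited form. As planned, the Zambian comparison of recent circumcision can be read as the effect of the distribution package as delivered, against SOC communities of which two also have VMMC listed. It cannot be read as the effect of self-testing alone.

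This rests on taking the Table 2 column to show mobiliser presence and on mobilisers raising circumcision; the document states neither outright. The apparent ratios of 1.16 to 1.59 show how far assumed multipliers of 1.25 to 2.0 would carry through. They do not estimate the actual bias. One secondary outcome in one of the two trials is affected.

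**What to change.** - State whether the Table 2 column records mobiliser presence before randomisation, and what it means for SOC communities.
- In Study objectives and in Outcome evaluation and measurement, word the circumcision result as the effect of the HIVST distribution package as delivered, with mobilisers in 6/6 HIVST and 2/6 SOC communities, and not as evidence on self-testing alone. Calling the contrast HIVST plus mobilisation versus SOC would misdescribe Mapanza and Lubuto.
- Adjust the circumcision analysis for each cluster's baseline circumcision prevalence. This deals with prior differences between communities but does not remove a continuing effect of mobilisers on new circumcisions.
- Add a sensitivity analysis adjusting for mobiliser presence. State beforehand that, with pairs kept, it is identified only by pairs 1 and 6 and is very imprecise. Analysing those two pairs on their own would be worse still, with 1 degree of freedom (critical t about 12.7).

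The cost is wording and analysis only: allocation is complete, and the baseline survey already collects the covariate. Each cluster-level term uses a degree of freedom, and the claim about circumcision becomes weaker.
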